## Abstract

**Background:**

Hepatocellular carcinoma (HCC) is a highly aggressive malignancy. Irreversible electroporation (IRE) is an ablative modality that uses high-voltage electrical pulses to permeabilize the cell membrane leading to cell necrosis. Unlike traditional thermal ablation, IRE is hardly affected by the “heat-sink” effect and can prevent damage of the adjacent vital structures. Nanosecond pulsed electric field (nsPEF) is a new IRE technique using ultra-short pulses (nanosecond duration), can not only penetrate the cell membranes, but also act on the organelles. Sufficient preclinical researches have shown that nsPEF can eliminate HCC without damaging vital organs, and elicit potent anti-tumor immune response.

**Objective:**

This is the first clinical study to evaluate feasibility, efficacy, and safety of nsPEF for the treatment of HCC, where thermal ablation is unsuitable due to proximity to critical structures.

**Methods and analysis:**

We will conduct an open-labeled, single-arm, prospective, multicenter, and objective performance criteria trial. One hundred and ninety-two patients with HCC, in which the tumor is located immediately (<0.5 cm) adjacent to the portal vein, hepatic veins, bile duct, gastrointestinal tract, or diaphragm, will be enrolled among 4 academic medical centers. The primary outcomes are the rate of complete ablation at 1 month and adverse events. Secondary outcomes include technical success, technique efficacy, nsPEF procedural characteristics, local tumor progression, and local progression-free survival.

**Ethics and dissemination:**

The trial will be conducted according to the ethical principles of the Declaration of Helsinki and has been approved by the ethics committee of all participating centers. The results of this study will be published in peer-reviewed scientific journals and presented at relevant academic conferences.

**Conclusions:**

This study is the Phase 1 clinical trial to evaluate the efficacy and safety of nsPEF in patients with HCC at high-risk locations where thermal ablation is contra-indicated. The results may expand the options and offer an alternative therapy for HCC.

**Clinical Trial Registration:**

ClinicalTrials.gov, identifier NCT04309747.

## 1 Introduction

Liver cancer is a major global health challenge that is predicted to affect more than 1 million individuals annually by 2025. Hepatocellular carcinoma (HCC) is the most common type of primary liver cancer (90%) and the fourth leading cause of cancer-related deaths worldwide (1). Local ablation is considered a potentially curative therapy for small HCC, as are surgical resection and liver transplantation (2, 3). Most ablation techniques, effected through radiofrequency, microwave, or laser, are based on thermal changes of the ablated tissue. However, many tumors cannot be treated with thermal ablation owing to hazardous tumor locations, and thermal damage to adjacent non-targeted structures can result in serious complications, such as hemorrhage, biliary fistula or intestinal perforation. Moreover, heat drawn away from the targeted tumor when it is adjacent to vessels, i.e., the heat sink effect, can result in incomplete ablation (4–6).

Irreversible electroporation (IRE) is a non-thermal ablation modality that has been advocated for solid hepato-pancreatico-biliary tumors. IRE delivers high-voltage electric pulses to permeabilize the cell membrane and consequently cause cell death, mostly by apoptosis (7, 8). Unlike thermal ablation, with IRE the extracellular connective tissue stays intact. This enables ablating tumors that are close to or involving vital structures such as the portal vein, hepatic veins, or bile duct. In addition, treatment efficacy of IRE is not impeded by heat sink effect (9–11). Based on these specific properties, IRE should be considered an ideal tool for patients for whom thermal ablation is too aggressive (12, 13).

Traditional IRE applies electric pulses of microsecond duration. Recently, a new type of IRE technique has been introduced, called nanosecond pulsed electric field (nsPEF). Unlike traditional microsecond duration IRE, the nsPEF with the duration from a few nanoseconds to hundreds of nanoseconds and the amplitude from 10 kV/cm to 300 kV/cm has been applied for tumor ablation. Since the duration shorter than the charging time constant of the cell membrane, nsPEF can not only penetrate the cell membranes, but also act on the organelles such as the endoplasmic reticulum, mitochondria, and nucleus (**Figure 1**). Cell responses to nsPEF include calcium mobilization (14), cytoskeleton destruction (15), activation of signaling pathways (16), and induction of apoptosis (17). Moreover,treatment with microsecond pulsed electric field has the undesirable side effect of adjacent skeletal muscle stimulation. Relatively long exposure of the skeletal muscle or its motor nerves to a high exogenous electric field will depolarize the cells and cause intense contractions. Previous studies found that shortening the time of the electric field exposure from microseconds to nanoseconds can reduce pain and involuntary muscle contraction (18). Therefore, different interaction mechanisms with traditional IRE, nsPEF expands the options and offers new opportunities for oncological therapy (**Table 1**).

**Figure 1 f1:**
[figure not shown]
The mechanisms of high-voltage electric pulses with microsecond or nanosecond duration.

**Table 1 T1:** Comparison of the mechanism of nsPEF and thermal ablation.

	nsPEF	RFA	MWA	Cryoablation
Fundamental principles	Utilizing high-frequency electric pulses penetrate the cell membranes, and act on the organelles	Utilizing high-frequency alternating current to generate heat	Utilizing electromagnetic waves to generate heat	Utilizing liquefied gases to induce the freezing–thawing cycle of targeted lesions
Treatment temperature	Nonthermal	60–100°C	>100°C	< – 40°C
Mechanism of tumor cell injury	Mainly apoptosis	Mainly necrosis	Mainly necrosis	Mainly necrosis
Advantages	Limited risk of thermal injury to neighbouring critical structures Unsensitive to heat sink effect	Well evaluated treatment	Higher and faster temperature picks reached than with RFA (less sensitive to heat sink effect than RFA)	Easy monitoring with imaging of ice ball progression
Limitations	General anesthesia Muscle contraction	Thermal injury of adjacent structure Heat sink effect	No reliable end point to set the amount of energy deposition	Cryoshock with first device

Killing cancer cells *in vitro via* nsPEF has been extensively explored, and successful tumor ablation has been demonstrated in various animal models, including malignant melanoma, skin basal cell carcinoma, lung squamous cell cancer and pancreatic cancer (17, 19–22). Most importantly, a clinical trial showed that nsPEF could successfully treat basal cell carcinoma in human patients, with significant efficacy and minimal invasion (23).

For the treatment of liver cancer, nsPEF has shown promising therapeutic prospects in both cell and animal experiments (**Supplementary Appendix 1**). Our preclinical studies have verified the efficacy of nsPEF, that is, that nsPEF can lead to long-term disease-free survival without recurrence (24, 25). In addition to inducing cell death, nsPEF inhibited cell proliferation and angiogenesis in tumors, triggered an immune response, and prevented secondary tumor growth (26–29).

Here, we propose to conduct the first-in-human trial to evaluate the efficacy and safety of nsPEF in patients with localized HCC, for whom thermal ablation is considered unsuitable.

## 2 Methods and Analysis

### 2.1 Study Design

This open-labeled, single-arm, prospective, multicenter trial will be conducted in 4 academic medical centers in China, as follows: First Affiliated Hospital, School of Medicine, Zhejiang University, Hangzhou; First Affiliated Hospital of Zhengzhou University, Zhengzhou; Shulan (Hangzhou) Hospital, Hangzhou; and First Affiliated Hospital of Xinjiang Medical University, Xinjiang. This trial has been approved by the committee for medical and health ethics of all the centers and registered on ClinicalTrials.gov (NCT04309747). The trial protocol is in accordance with all the recommendations of the SPIRIT (Standard Protocol Items: Recommendations for Interventional Trials) 2013 statement (30). Written informed consent will be obtained from all participants prior to enrollment. The flow diagram of the study is presented in **Figure 2**.

**Figure 2 f2:**
[figure not shown]
Flow chart of study. *Contrast-enhanced MRI will be performed 1 month after the procedures to evaluate technique efficacy. In the event of incomplete ablation, an additional nsPEF procedure will be conducted with the same technique. If the residual tumor is still viable after the second session, then nsPEF is considered failed, and the patient will be excluded from the trial and referred to other therapies. HCC, hepatocellular carcinoma; nsPEF, nanosecond pulsed electric field; MRI, magnetic resonance imaging.

### 2.2 Patient Population

Potential trial participants will be identified at an institutional multidisciplinary tumor board, comprised of interventional radiologists, hepatobiliary surgeons, medical oncologist, and diagnostic radiologists. The potential subjects will subsequently be referred for enrollment and eligibility screening. All candidates will be reviewed for safety and eligibility by an experienced interventional radiologist, participating in the research project at each center. All eligible patients will be explained about the study protocol in details. Only those who sign the consent form will enter the trial. The inclusion and exclusion criteria are listed in **Table 2**.

**Table 2 T2:** Patients inclusion and exclusion criteria.

Inclusion criteria	Exclusion criteria
HCC diagnosed histologically or clinically according to the guidelines of the American Association for the Study of Liver Diseases tumors located immediately (<0.5 cm) adjacent to the portal vein, hepatic veins, bile duct, gastrointestinal tract, or diaphragm age ≥ 18 years no evidence of extrahepatic metastasis single tumor with a maximum diameter of ≤5cm, or the number of tumors of ≤3 and a maximum diameter of ≤3cm. Child-Pugh A or B Performance status according to Eastern Cooperative Oncology Group (ECOG) ≤2. written informed consent	Ventricular cardiac arrhythmia Congestive heart failure, NYHA Class ≥ 3 Active coronary artery disease History of epilepsy Any implanted stimulation device Other treatment <6 weeks prior to treatment presence of vascular invasion or extrahepatic metastasis. Severe coagulation abnormalities

### 2.3 Baseline Characteristics

Standard evaluation of the patient before the nsPEF procedure should include a general health history review (demographics, past medical history, allergies, and medications), assessment of performance status and pain, general anesthetic review, electrocardiogram, echocardiography, and laboratory tests (blood routine examination, blood coagulation, liver function, tumor marker, and myocardial enzyme). All included patients will have a pre-intervention radiological assessment within 4 weeks before the nsPEF procedure, including abdominal contrast-enhanced magnetic resonance imaging (MRI), CT angiography of the liver, chest computed tomography (CT), contrast-enhanced ultrasound (CEUS) of the liver, and abdominal contrast-enhanced CT when MRI is contraindicated.

### 2.4 Interventions

The nsPEF procedure will be performed under general anesthesia with endotracheal intubation. Intraoperative nondepolarizing neuromuscular blocking agents (rocuronium or cis-atracurium) will be applied in combination to achieve deep muscle relaxation, in which no muscle tremor visible to the naked eye or a train of four stimulations (TOF) is 0. Deep muscle relaxation can eliminate the muscle contractions caused by the high-voltage pulsed electric fields and reduce the injuries of the target organs due to electrode displacements.

The nsPEF procedure will be guided by CT or US. The nsPEF therapeutic apparatus manufactured by the Hangzhou Ruidi Biotech Ltd company (Hangzhou, Zhejiang, China) (**Figure 3**) will be used in this study. All electrodes will be placed parallel by trained interventional radiologists with extensive experience in percutaneous thermal ablation (via radiofrequency, microwave, or laser) and nonthermal ablation (IRE). Depending on the individual tumor size and shape, 2 to 6 19-gauge unipolar nsPEF electrodes with an appropriate active tip length of 1.0 to 2.0 cm will be placed 1.0 to 2.5 cm apart using ultrasound guidance. The nsPEF device generates 15 to 30 kV pulses, and voltage will be determined by a standard algorithm that uses factors such as the intended size of the ablation zone, the number of electrodes, the distance between electrodes, and the length of the active electrode tip (**Figure 4**). Once the electrodes are correctly placed, a test pulse at 5 kV will be delivered. After the test pulse confirms adequate conductivity, nsPEF will be conducted with 800 pulses, a pulse length of 300 ns, with electrocardiographic triggering.

**Figure 3 f3:**
[figure not shown]
Nanosecond pulsed electric field equipment (Hangzhou Ruidi Biotech Ltd, Hangzhou, Zhejiang, China) **(A)** console. **(B)** displayer. **(C, D)** 19G monopolar needle electrodes.

**Figure 4 f4:**
[figure not shown]
The nsPEF procedure strategy. Depending on the individual tumor size and shape, 2 to 6 19-gauge unipolar electrodes with an appropriate active tip length of 1.0 to 2.0 cm will be placed 1.0 to 2.5 cm apart using ultrasound guidance. The nsPEF will be conducted with 800 pulses of 300ns duration, and an electric field of 15 to 30 kV. nsPEF, nanosecond pulsed electric field.

After completion of the pulse applications, CEUS will be performed to confirm sufficient ablation, which is defined as an ablation zone that includes the entire target tumor and a safety margin of at least 0.5 cm. If the extent of the ablation zone is suspected insufficient, additional cycles of energy depositions for overlapped ablations will be performed, preferably after electrodes pullbacks (from 1 to 2 cm partial withdrawal of needles along the axis of the initial puncture) and/or partial or complete electrodes reinsertion (in different axis from initial puncture). A case is shown in **Figure 5** and **Video 1**.

### 2.5 Postprocedural Follow-Up

After the procedure, all patients will be monitored for at least another day in inpatient department, in accordance with current medical practice. Routine laboratory studies, electrocardiogram, and CEUS will be performed to assess procedure-related complications.

Contrast-enhanced MRI will be performed 1 month after the procedures to evaluate technique efficacy. Complete ablation is considered complete nonenhancement of the treated tumor, and incomplete ablation is the presence of residual tumor on contrast-enhanced MRI. In the event of incomplete ablation, an additional nsPEF procedure will be conducted with the same technique. If the residual tumor is still viable after the second session, then nsPEF is considered failed, and the patient will be excluded from the trial and referred to other therapies.

If efficacy is confirmed, then clinical, biological, and radiological examinations are required every 3 months during the first year, and once every 6 months thereafter. Baseline and follow-up images will be interpreted independently by all experienced diagnostic abdominal radiologists. At the end of the trial, 2 independent radiologists will review all images before and after treatment, and reach a consensus.

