#### 2.6.1 Primary Outcomes

The primary outcomes are the complete ablation rate at 1 month, and adverse events. The later may be device-related, intraprocedural, postprocedural, or late, and will be reported using the NCI Common Terminology Criteria for Adverse Events (CTCAE) (**Supplementary Appendix 2**).

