#### 2.6.2 Secondary Outcomes

The secondary outcomes are the following: technical success, technique efficacy, characteristics of the nsPEF procedure, local tumor progression (LTP), and local progression-free survival (LPFS). Specifically, technical success addresses whether the tumor is treated according to protocol and covered completely by the ablation zone; tumor coverage will be assessed immediately after the nsPEF procedure by CEUS.

Technique efficacy is regarded as radiologic complete ablation achieved after as many as 2 iterative nsPEF procedures. The nsPEF procedure characteristics include the following: number of electrodes used; active tip length of the electrodes; distance between electrodes; rate of pullback applications; total number of pulses delivered per procedure; total procedural time; ablation time; ablation volume; and sufficient ablative margin.

LTP describes the reappearance of HCC adjacent to the ablated zone after successful treatment. LPFS is defined as the time from the commencement date of the nsPEF procedure to the date of local progression. LPFS will be censored at the date of the last follow-up, when the patient has no evidence of local progression.

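### Removing patients with viable tumour after the second session keeps treatment failures out of LPFS events and out of scheduled late safety follow-up

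*Protocol article*

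**What the plan says.** Section 2.5 (Postprocedural Follow-Up) has a contrast-enhanced MRI at 1 month and a second nsPEF procedure if ablation is incomplete. If tumour remains viable after that, "then nsPEF is considered failed, and the patient will be excluded from the trial and referred to other therapies". The Figure 2 legend gives the same rule: "If the residual tumor is still viable after the second session, then nsPEF is considered failed, and the patient will be excluded from the trial".

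Section 2.5 then makes later follow-up depend on success: "If efficacy is confirmed, then clinical, biological, and radiological examinations are required every 3 months during the first year", and every 6 months after that.

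The outcomes touched by this are:

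- **Primary (Section 2.6.1).** "The primary outcomes are the complete ablation rate at 1 month, and adverse events". On adverse events it adds: "The later may be device-related, intraprocedural, postprocedural, or late".
- **LPFS (Section 2.6.2).** "LPFS is defined as the time from the commencement date of the nsPEF procedure to the date of local progression". Patients without evidence of local progression are censored at last follow-up. The status of a patient whose tumour never became non-viable is not given.
- **Technique efficacy (Section 2.6.2).** Complete ablation on imaging after at most two procedures.
- **LTP (Section 2.6.2).** Reappearance after successful treatment, so limited to successes by definition.

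Section 2.8 analyses adverse events and LPFS per patient, and technique efficacy per tumour.

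**The concern.** Exclusion is triggered by the outcome the trial measures. LTP is openly conditional on success, but LPFS is not: its clock starts at the procedure for everyone treated. Removing the patients in whom local treatment failed turns it into an estimate among responders. Any responder also has an event-free period up to the confirming MRI by construction.

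Late safety is affected separately. Late events are part of a primary outcome in a first-in-human trial, and the excluded patients have had two sessions. An analysis plan could settle how they are counted, but it could not recover late events that no visit was scheduled to collect.

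**Working it through.** **No plan figure to reproduce.** The article gives no expected LPFS, second-session success rate or progression hazard. Two of its figures are used as inputs: 80% complete ablation at 1 month and 192 enrolled (160 x 1.2), both from Section 2.7.

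**Assumptions.**

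- One tumour per patient. The 80% is stated per tumour and Table 2 admits up to three tumours, so using it per patient is a simplification.
- First-session success p1 = 0.80.
- Second-session success p2 = 0.30 to 0.70 (not in the documents).
- Local progression hazard among successes 0.15 per year, counted from the procedure (not in the documents).
- The MRI after the second session falls within the first year.

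**Step 1: share of patients excluded.** f = (1 - p1)(1 - p2).

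| p2 | f | Of 192 |
|---|---|---|
| 0.30 | 0.20 x 0.70 = 14% | 26.9 |
| 0.50 | 0.20 x 0.50 = 10% | 19.2 |
| 0.70 | 0.20 x 0.30 = 6% | 11.5 |

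**Step 2: 1-year LPFS.** Among successes, S = exp(-0.15) = 0.861. Over all treated patients, with technique failure as an event, LPFS = (1 - f) x S.

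| f | LPFS with failures left out | LPFS with failures as events |
|---|---|---|
| 14% | 86.1% | 0.86 x 0.861 = 74.0% |
| 10% | 86.1% | 0.90 x 0.861 = 77.5% |
| 6% | 86.1% | 0.94 x 0.861 = 80.9% |

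Censoring failures at exclusion, instead of dropping them, does not remove the bias. They add time at risk but no events, so the curve is the same or slightly higher.

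**Step 3: sensitivity to the hazard.** The gap is S - (1 - f)S = f x S. If 1-year LPFS among successes is anywhere from 70% to 90%, the gap runs from 0.06 x 0.70 = 4.2 to 0.14 x 0.90 = 12.6 percentage points. The direction does not depend on the assumptions; only the size does.

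**Step 4: technique efficacy.** With failures kept, it is p1 + (1 - p1)p2 = 1 - f, which is 86%-94%. If exclusion also removes them from the denominator, every remaining case is a success and the rate is 100% by construction.

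**Step 5: late safety.** Setting the rule in Section 2.5 beside Section 2.6.1, the 6%-14% excluded have no scheduled examination after the assessment that shows failure, while late events remain part of a primary outcome.

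**The case against.** The best counter-argument is that exclusion means only leaving study treatment, that calling nsPEF failed already records the failure, and that analysis sets belong in an analysis plan that is not shown. This is a fair reading for technique efficacy, since deleting its failures would make the outcome meaningless. It does not rescue LPFS or late safety. The rule removes the patient from the trial, it is stated twice, and the follow-up schedule is tied to confirmed efficacy. That is a stated rule, not brevity.

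It is also true that the LPFS text is silent on persistent tumour, and that counting it as an event is a common convention but not the only one. As written, however, nothing makes it an event.

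Two stronger inferences are tempting, and the documents do not support them:

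- **The primary complete ablation rate is inflated.** A reader might compute 0.80/0.90 = 89% in place of 80%. But the 1-month MRI comes before the second session and therefore before exclusion, and Section 2.7 states its hypothesis for tumours treated. Inflation would require deleting a result already recorded, and nothing in the article says this is done.
- **Late safety is lost in the patients with the most nsPEF exposure.** Patients who succeed at the second session have also had two procedures, and they stay in follow-up. Excluded patients still have the immediate post-procedure checks, and Section 2.9 sets no time limit on serious adverse event reporting. The gap is in scheduled late follow-up, and later therapies would complicate attribution there.

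**Conclusion.** The point holds for LPFS and for late safety. On the stated assumptions, about 12-27 of 192 patients leave the trial because treatment failed, and 1-year LPFS reads 86% instead of about 74%-81%. The upward direction follows from the text alone. The size rests on one tumour per patient, the assumed second-session success and the assumed hazard. With several tumours per patient and the same per-tumour rate, a patient is at least as likely to have one that fails.

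For technique efficacy the point is conditional: the rate is 100% by construction only if exclusion also means removal from the denominator. For the 1-month complete ablation rate, all that is needed is a sentence confirming the denominator. LTP is unaffected.

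**What to change.** 1. In Section 2.5 and the Figure 2 legend, replace the exclusion wording with a statement that nsPEF is counted as failed and the patient stays in trial follow-up. Referral to other therapies is unchanged.
2. State that all treated tumours stay in the denominators for complete ablation and technique efficacy, and all treated patients in those for adverse events and LPFS.
3. In Section 2.6.2, count technique failure as an LPFS event, dated at the MRI after the second session that shows viable tumour. If LPFS in responders is also wanted, start it at confirmed complete ablation and label it as such.
4. Continue scheduled late adverse event collection in these patients, and record subsequent therapy so that attribution can be judged.

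The cost is a short amendment, continued follow-up of about 12-27 patients on the assumptions above, and a less favourable reported LPFS. The amendment should come before such patients leave follow-up, because late events not collected may not be recoverable.
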